### **Pentaglobin**

IgM enriched intravenous immunoglobulin (IgGAM) may play a role in modulating an immune system that is in a hyperinflammatory state. Tailored therapy in stage IIb hinges on the use of immunomodulatory agents to reduce systemic inflammation before it overwhelmingly results in multi-organ dysfunction.

Rodriguez et al. 2005 showed in a prospective, randomized, double-blind, multicentre clinical study with 56 patients the effectiveness of Pentaglobin® (IgGAM) in patients with peritonitis and severe sepsis / septic shock (72).

According to a 2007 meta-analysis, 8 studies performed with IgGAM on 560 patients showed a pooled relative risk of death of 0.64, whereas the pooled effect of 7 studies performed with IVIG on 932 patients was 0.85 (73).

Nevertheless, there is still insufficient data, so that experts - in relation to the above meta-analysis - are only able to pronounce a grade C recommendation in the German sepsis guidelines for IgGAM. No more recent data are available. This study is therefore intended to significantly expand the data on adjunctive therapy with IgGAM in severe pneumonia and ARDS in COVID-19.

## 6 STUDY OBJECTIVES

The overall objective of this trial is to identify effective and safe treatments for SARS-CoV-2 infection. Various treatments are currently already used, although data on their efficacy for SARS-CoV-2 are lacking. These treatments will be compared with each other in this randomized controlled trial.

### 6.1 Primary objective

To investigate the efficacy of various experimental therapeutics for patients with laboratory-proven SARS-CoV-2 infection. A 7-category ordinal scale for clinical severity assessment as proposed by the World Health Organization will be used for efficacy assessment:

- Time to sustained (>48h) improvement of one category from admission
- Clinical status, assessed once daily
- Mean change in the ranking on an ordinal scale from baseline (assessed once daily)

### 6.2 Secondary objectives

- To assess efficacy according to the National Early Warning Score (NEWS Score): time to
  - Time to discharge or to a NEWS score of  $\leq 2$  and maintained for 24 hours, whichever occurs first
  - Change from baseline until day 29, discharge or death, assessed once daily
- Oxygenation
  - Oxygenation free days until day 29
  - Incidence and duration of new oxygen use during the trial
- Mechanical Ventilation
  - Ventilator free days until day 29
  - Incidence and duration of new mechanical ventilation use during the trial
- Viral load/viral clearance using PCR-based assays.
- Hospitalization
  - Duration of hospitalization
  - Duration of intensive care unit treatment
  - Intensive care unit admissions
- Mortality
  - 15-day, 29-day, day 60 mortality, day 90 mortality
- Sub-Study A: number of thromboembolic events
- Exploratory assessment of transaminases (including alkaline phosphatase, gamma-glutamyltransferases (GGT), aspartate aminotransferase (ASAT), alanine aminotransferase (ALAT)) and liver function parameters (including bilirubin, prothrombin time, international normalized ratio, albumin, fibrinogen) and their course during the disease and treatment
- An exploratory endpoint will encompass a comprehensive assessment of inflammatory parameters and their changes during treatment and wash out time, as well as exploratory genotype and RNA analysis with a focus on inflammation, coagulation, and the specific pathophysiology of the disease (if possible for center).

- Within all patients, the impact of obesity and associated diseases on mortality will be investigated
- Safety
  - Cumulative incidence of serious adverse events
  - Discontinuation or temporary suspension of therapy
  - Changes in white cell count, hemoglobin, platelets, creatinine, glucose, total bilirubin, alanine aminotransferase (ALT), aspartate aminotransferase (AST), uric acid over time
  - Occurrence of drug induced liver injury (DILI) in various treatment arms
  - Sub-study A: bleeding events
- Treatment Arm 2: Analysis of CYP3A4 interaction of lopinavir/ritonavir with other prescribed medication in a retrospective manner
- Sub-study B: To investigate clinical outcomes (blood pressure, dyspnea, body temperature, patient-reported fear/anxiety) and the RAS-fingerprint of patients with SARS-CoV-2 infection and arterial hypertension randomized to RAS blocking (“stay-on-any-RAS-blockade” for those patients with previously treated hypertension; candesartan for those with blood pressure  $\geq 140/90$ , measured twice after SARS-CoV-2 infection) versus non-RAS blocking treatment (nitrendipine or doxazosin).
- Sub-study C: modified SOFA score,  $paO_2/FiO_2$  ratio, or  $SpO_2/FiO_2$  ratio
- Pharmacokinetics of antiviral substances, if assays are available (e.g. trough level analysis of lopinavir/ritonavir)
- Sub-Study C for Pentaglobin: CRP, PCT, IL-6, differential blood count (baseline and day 2, 3, 7), IgM, IgA and IgG-levels (baseline, day 2, 3, 4, 5), modified SOFA score (baseline, on day 7 and day 28 of study participation)

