### 7.1.2 Inclusion criteria

- Laboratory confirmed (i.e. PCR-based assay) infection with SARS-CoV-2 (ideally but not necessarily  $\leq 72$  hours before randomization for “antiviral” treatments) OR radiological signs of COVID-19 in chest X-ray or computed tomography
- Hospitalisation due to SARS-CoV-2 infection, except for sub-study B, which may also include outpatients with COVID-19
- Requirement of oxygen support (due to oxygen saturation  $<94\%$  on ambient air or  $>3\%$  drop in case of chronic obstructive lung disease)
- Informed Consent obtained, the patient understands and agrees to comply with the planned study procedures, except for sub-study C: obtaining informed consent may be impossible due to the severe condition of the patient and may be waived
- $\geq 18$  years of age
- Sub-study A: not on chronic anticoagulation
- Sub-study B: Sub-study B: blood pressure  $\geq 130/85\text{mmHg}$  in 2 consecutive measurements OR patients with established and treated hypertension
- Sub-study B: Control group 1: Patients with suspicion of but negative tests for COVID-19. This group may consist of hospitalized and non-hospitalized patients.
- Sub-study B: healthy volunteers
- Sub-study C: Signs of respiratory deterioration and progressing inflammation: need for oxygen supplementation, non-invasive ventilation, high-flow oxygen devices or mechanical ventilation AND CRP levels  $>5\text{mg/dL}$  (for Pentaglobin only) and ICU admission (for Pentaglobin only)
- For female patients with childbearing potential: willingness to perform effective measures of contraception during the study.

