- Exploratory assessment of transaminases (including alkaline phosphatase, gamma-glutamyltransferases (GGT), aspartate aminotransferase (ASAT), alanine aminotransferase (ALAT)) and liver function parameters (including bilirubine, prothrombin time, international normalized ratio, albumin, fibrinogen) and their course during the disease and treatment
- an exploratory endpoint will encompass a comprehensive assessment of inflammatory parameters and their changes over treatment and wash out time, as well as exploratory genotype and RNA analysis with a focus on inflammation, coagulation, and the specific pathophysiology of the disease.
- Sub-study C: modified SOFA score, paO2/FiO2 ratio, or SpO2/FiO2 ratio

For **binary secondary endpoints** (such as 15 and 29 day mortality, incidence rates) absolute (n= ) and frequencies in percent (%) will be calculated per treatment group. 95%-confidence intervals will be calculated for rates, if appropriate. Such data will be visualized with bar charts. If appropriate, logistics regression model will be applied using treatment as independent factor. Furthermore, the model will be adjusted for sex and age.

For **ordinally scaled endpoints** (such as clinical status on day 3, 5, 8, 11 and 29 after admission) absolute (n= ) and frequencies in percent (%) will be calculated for all categories separately for each treatment group. Treatment groups will be compared with each other

**Continuous secondary endpoints** such as “days free of Oxygenation free days within 29” and “Ventilator free days until day 29 days” will be summarized by mean, standard deviation (SD), median, first and third quartiles, minimum and maximum for each treatment arm separately. These secondary endpoints will be analysed using an analysis of covariance (ANCOVA) using the factor treatment adjusting for the factors Sex and the covariate Age (in Years). Mean estimates will be provided, together with their corresponding two-sided 95% confidence intervals. We will conduct further explorative analyses adjusting for calendar time in the models concerned to account for time trends (e.g. severity of cases might change over time).

For **time to event endpoints** (such as time to discharge or to a NEWS of  $\leq 2$  and maintained for 24 hours, whichever occurs first) we will provide similar analyses as described for the primary endpoint.

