## 15 Appendix I National Early Warning Score (NEWS)

| Physiological Parameters | 3   | 2      | 1       | 0       | 1       | 2       | 3          |
|--------------------------|-----|--------|---------|---------|---------|---------|------------|
| Respiration rate         | ≤8  |        | 9-11    | 12-20   |         | 21-24   | ≥25        |
| Oxygen saturation        | ≤91 | 92-93  | 94-95   | ≥96     |         |         |            |
| Any supplemental oxygen  |     | yes    |         | no      |         |         |            |
| Temperature              | ≤35 |        | 35.1-36 | 36.1-38 | 38.1-39 | ≥39     |            |
| Systolic BP              | ≤90 | 91-100 | 101-110 | 111-219 |         |         | ≥220       |
| Heart rate               | ≤40 |        | 41-50   | 51-90   | 91-110  | 111-130 | ≥131       |
| Level of consciousness   |     |        |         | A       |         |         | V, P, or U |

National Early Warning Score (NEWS) (82), A = Alert, V = verbal response or voice, P = painful stimuli or pain, U = unresponsive

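### The NEWS time-to-event secondary endpoint can already be met at randomization, so some unchanged patients count as events within about the first 24 hours (minor)

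*Protocol*

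**What the plan says.** The synopsis (objectives and efficacy endpoints), section 6.2 and section 11.6.2 all give the same event: "Time to discharge or to a NEWS score of $\leq 2$ and maintained for 24 hours, whichever occurs first". Section 11.6.2 names it as its example of a time-to-event endpoint ("such as time to discharge or to a NEWS of $\leq 2$ and maintained for 24 hours, whichever occurs first") and gives it analyses like those of the primary endpoint, which are Kaplan-Meier plots, a log-rank test and a Cox model.

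Section 7.1.2 makes oxygen need an entry condition: "Requirement of oxygen support (due to oxygen saturation" below 94% on ambient air, or a drop of more than 3% in chronic obstructive lung disease. Neither section 7.1.2 nor section 7.1.3 sets a minimum NEWS.

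Appendix I scores oxygen use as "Any supplemental oxygen | | yes | | no", where yes stands in the 2-point column and no in the 0-point column. It scores saturation as "Oxygen saturation | ≤91 | 92-93 | 94-95 | ≥96", running from 3 points down to 0, and does not separate values on air from values on oxygen.

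Section 11.6.1 defines the primary endpoint as improvement against the status at randomization. The NEWS endpoint has no such clause.

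**The concern.** A time-to-event endpoint for improvement should start from patients who have not yet had the event. Here the threshold of 2 equals the points that Appendix I gives for oxygen use alone, and oxygen need is what makes a patient eligible. A stable patient whose other items are all normal therefore sits at the threshold on entry and has only to stay there for a day.

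Such an event is fixed by baseline status. It cannot reflect treatment, yet it enters the Kaplan-Meier curve and the log-rank test as an early event and removes from the risk set a patient who could later have shown a difference. The patient may still be in WHO category 4, or in category 5 on high-flow oxygen. At stake is the sensitivity of one exploratory comparison and how its curve is read.

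**Working it through.** **Inputs.** The event definition comes from sections 6.2 and 11.6.2, the entry condition from section 7.1.2, and the scoring from Appendix I. Section 8.5.3 has NEWS obtained daily, and Table 1 schedules it at screening and at randomization.

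**1. Lowest score on oxygen.** Oxygen use gives 2. Each of the other six items can score 0: respiration 12-20, saturation 96 or more, temperature 36.1-38, systolic pressure 111-219, heart rate 51-90, alert. The minimum is 2 + 0 + 0 + 0 + 0 + 0 + 0 = 2, which satisfies the threshold.

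**2. How narrow the profile is.** With oxygen fixed at yes, the bands give 5 × 4 × 5 × 5 × 6 × 2 = 6000 combinations (respiration, saturation, temperature, systolic pressure, heart rate, consciousness). Exactly one totals 2 or less, namely the one in step 1. One more point, for example saturation 94-95 or heart rate 91-110, gives 3 and fails. This counts band combinations and says nothing about how many patients fall in each.

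**3. Lowest score on room air.** For an eligible patient scored on air with saturation below 94, the bands give 5 × 2 × 5 × 5 × 6 × 2 = 3000 combinations. Again exactly one qualifies: saturation 92-93 (2 points) with all else normal, total 2.

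**4. Timing.** The score must be held: "and maintained for 24 hours, whichever occurs first". With daily scoring, that is at least two consecutive daily scores. An unchanged patient with either profile has the event at 0 h if it is dated at the start of the hold, or at about 24 h if dated at its end. The protocol does not say which.

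**5. Illustration of dilution.** The protocol gives no design figures for this endpoint, so those of the primary endpoint in section 11.2 are borrowed: 200 patients, 154 events, hazard ratio 1.6. The section 11.2 power is reproduced first:

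- Power = Φ(√(154/4) × ln 1.6 − 1.960) = Φ(2.916 − 1.960) = 83.05%, against 83.15% stated.

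Let a share f, equal in both arms, have the event at the outset.

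- Variance from these events: V0 = (200f/4) × (200 − 200f)/199.
- Variance from the remaining events: V1 = 154(1 − f)/4.
- All patients: power = Φ(V1 × ln 1.6/√(V0 + V1) − 1.960).
- Those patients excluded: power = Φ(√V1 × ln 1.6 − 1.960).

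For f = 10%: V0 = 5 × 180/199 = 4.52 and V1 = 34.65. All patients: Φ(16.29/6.26 − 1.960) = 74%. Excluded: Φ(2.767 − 1.960) = 79%.

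| Assumed share f | Power, all patients | Power, those patients excluded |
|---|---|---|
| 0% | 83% | 83% |
| 5% | 79% | 81% |
| 10% | 74% | 79% |
| 20% | 64% | 74% |
| 30% | 54% | 68% |

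Every f above 0 is an assumption.

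**6. Temperature bands.** Appendix I places 39.0 both in the 1-point band (38.1-39) and in the 2-point band (39 or more). For a patient on air with one point elsewhere, NEWS is then 2 or 3, which decides whether the threshold is met. A patient on oxygen is at 3 or more under either reading.

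**The case against.** The strongest case is that little depends on this. Section 11.6.2 calls all secondary analyses exploratory, with p-values and intervals for description only. The profile is narrow and must last a day, and section 7.1.3 excludes patients expected to be discharged within 48 hours, which removes some of the mildest. NEWS change from baseline, oxygenation-free days and the primary endpoint already measure change and oxygen dependence. Section 7 says the choice of endpoints was based on the WHO master protocol. All of this stands, and it limits the point to minor.

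It may also be said that handling patients already at the threshold belongs in the SAP. How the hold is dated can be left there. The event itself cannot, because the protocol states it in full in several places and, applied as written, it counts baseline status as an event. If the SAP already restricts the analysis, the protocol needs only to be aligned with it.

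A reader might go further and infer that unchanged patients are declared recovered at time zero, and that the 6-day median difference shrinks. The documents support neither. The protocol does not call this endpoint recovery, and the event may fall at about 24 h. The 16- and 10-day medians belong to the primary endpoint. If they are borrowed anyway with shares of 10%, 20% and 30% at time zero, the medians are ln((1 − f)/0.5)/λ with λ = ln 2/16 and ln 2/10: 13.6/8.5, 10.8/6.8 and 7.8/4.9 days. The gap in days falls to 5.1, 4.1 and 2.9, but the ratio of medians stays at 1.6.

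**Conclusion.** The point holds. On the protocol's own table, two baseline profiles of eligible patients already meet the NEWS threshold, and neither a baseline clause nor an eligibility rule prevents it. If unchanged, those patients have the event within about 24 hours of randomization. With randomization, the affected share is expected to be equal between arms, so the effect is dilution and not bias towards either arm.

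The size is unknown, because the share of patients at NEWS 2 or less at entry is not in the documents. The power figures rest on assumed shares and on design figures borrowed from another endpoint, and they show direction only. The primary endpoint is unaffected, since it is measured against status at randomization. The overlap at 39.0 degrees is a separate slip and adds no weight. Severity: minor.

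**What to change.** In section 11.6.2, analyse this endpoint in patients whose baseline NEWS, the last score at or before randomization, is above 2. Report the number per arm already at 2 or less, and keep the all-patient analysis as supportive. Table 1 already schedules the score at screening and randomization, so no new data are needed. Because the restriction uses a value from before treatment allocation, it does not bias the comparison. The cost is fewer patients in this one analysis, for example 180 of 200 if the share were 10%.

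A version requiring NEWS of 2 or less without supplemental oxygen may be added as a sensitivity analysis. It should not replace the definition: a patient scored on room air at saturation 92-93 would still qualify at baseline, and it departs from the endpoint set that section 7 bases on the WHO master protocol.

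In Appendix I, make the two upper temperature bands disjoint so that 39.0 has one score. This is a change of wording only.

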|  | 
 
▪ Time to discharge or to a NEWS of <math>\leq 2</math> and maintained for 24 hours, whichever occurs first
 
▪ Change from baseline (assessment once daily)
 
- Oxygenation 
 
▪ Oxygenation free days until day 29
 
▪ Incidence and duration of new oxygen use (e.g. oxygen insufflation, high-flow oxygen, non-invasive ventilation, mechanical ventilation, etc.) during the trial
 
 
 
- Viral clearance
 
- Duration of hospitalization, of ICU treatment and number of ICU admissions
 
- Mortality at day 15, 29, day 60 and day 90
 
- Sub-Study A: number of thromboembolic events
 
- Sub-study B: To investigate the RAS and bradykinin fingerprint of patients with SARS-CoV-2 infection, with and without RAS blocking treatment, as specified above; to investigate blood pressure, dyspnea, body temperature, fear/anxiety (subject to availability of samples)
 
- Within all patients, the impact of obesity and associated diseases on mortality will be investigated (e.g. mortality, inflammatory response, duration of hospitalization, intensive care unit admission, new oxygen use, duration of oxygen)
 
- Exploratory assessment of transaminases (including alkaline phosphatase, gamma-glutamyltransferases (GGT), aspartate aminotransferase (ASAT), alanine aminotransferase (ALAT)) and liver function parameters (including bilirubin, prothrombin time, international normalized ratio, albumin, fibrinogen) and their course during the disease and treatment
 
- An exploratory endpoint will encompass a comprehensive assessment of inflammatory parameters and their changes during treatment and wash out time, as well as exploratory genotype and RNA analysis with a focus on inflammation, coagulation, and the specific pathophysiology of the disease (if possible for center).
 
- Sub-study C: modified SOFA score, <math>paO_2/FiO_2</math> ratio, or <math>SpO_2/FiO_2</math> ratio
 
- Substudy C, Pentaglobin part: CRP, PCT, IL-6, differential blood count (baseline and day 2, 3, 7), IgM, IgA and IgG levels (baseline, day 2, 3, 4, 5), modified SOFA score (baseline, day 7 and day 28)
 
 |

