Dexamethasone treatment reduced 28-day mortality in patients receiving oxygen and in patients requiring invasive ventilation (56). Since only such patients will be eligible for this trial, all patients may receive dexamethasone, based on the judgement of the treating physicians or local standard of care. Overall, the observed effect sizes of dexamethasone, but also of remdesivir, as discussed in detail, were relatively small and many patients still required intensive care or even died within these trials. Therefore, more effective treatments are still desperately required, which is why this study will also continue to recruit patients.

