## 8.2 Randomization and stratification

This is a randomized trial with different active treatments. However, for this platform trial, some special circumstances need to be considered. In the “Main” antiviral study three treatment options remain active within the randomized trial. Sub-study A, B, C, will also be conducted as randomized trials against standard of care. Randomization will be carried out online by [www.meduniwien.ac.at/randomizer](http://www.meduniwien.ac.at/randomizer). No stratification will be applied, except for the asunercept part of the trial. Based on the currently known risk factors, hospitalized patients are probably older and have more comorbidities, compared to a “general population”. Moreover, the sample sizes are relatively small, which precludes further stratification due to statistical reasons.

For sub-study B randomization will occur within the treatment group. In this cohort (labelled as “sub-study B”), patients with established arterial hypertension (and treatment) may be switched and patients with blood pressure  $\geq 130/85$  mmHg will be randomized to new treatments. Importantly, those patients with blood pressure  $\geq 130/85$  mmHg but  $< 140/90$  mmHg, who are randomized to non-RAS blocking treatment will not receive any treatment. Patients will be randomized to the following two treatment options using an allocation ratio of 1:1

- RAS blocker containing treatment (candesartan)
- Non-RAS blocker containing treatment (e.g. nitrendipin/amlodipin/doxazosin)

Thus, clinicians may decide within the first 24 hours if patients who participate in the main antiviral study A will also fulfill the criteria for one of the sub-studies. It is currently not intended to simultaneously enroll a patient in sub-studies A or B. Within sub-studies randomization will be done using the same software.

For sub-study C:

Asunercept: a 3:1 randomization against standard of care will be done, whereas three different doses of asunercept will be tested. Stratification according to the WHO scale at screening will be performed (only WHO scales 4, 5, and 6 are available for inclusion (patients with oxygen demand).

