### 11.6.2 Secondary endpoint analysis

- Clinical Status of patients according to the above-mentioned WHO scale:
  - Time to improvement of one category from admission
  - Clinical status daily
  - Mean change in the ranking on an ordinal scale from baseline
- National Early Warning Score (NEWS):
  - Time to discharge or to a NEWS of  $\leq 2$  and maintained for 24 hours, whichever occurs first
  - Change from baseline
- Oxygenation
  - Oxygenation free days until day 29
  - Incidence and duration of new oxygen use during the trial
- Mechanical Ventilation
  - Ventilator free days until day 29
  - Incidence and duration of new mechanical ventilation use during the trial
- Viral load/viral clearance
  - Baseline, and three times a week until infection has resolved
- Hospitalization
  - Duration of hospitalization
  - Duration of intensive care unit treatment
  - Intensive care unit admissions
- Mortality
  - 15-day, 29-, 60-day mortality
- Within all patients, the impact of obesity and associated diseases on mortality will be investigated (e.g. mortality, inflammatory response, duration of hospitalization, intensive care unit admission, new oxygen use, duration of oxygen)
- Treatment arm 2: drug-drug interaction analysis with lopinavir/ritonavir, in a retrospective manner
- pharmacokinetics of antiviral substances, if assays are available (e.g. lopinavir/ritonavir trough level analysis)
- Sub-study A: thromboembolic events

- Sub-study B: Renin Angiotensin System (RAS) fingerprint in patients with SARS-CoV-2 infection randomized to no RAS blocking agents, randomized to angiotensin converting enzyme (ACE) inhibitor treatment and randomized to angiotensin II blockade
  - Quality of life: EuroQoL- 5 Dimension (EQ-5D)
  - Activities of daily living/life participation, Instrumental activities of daily living scale (IADLS)
  - PROMIS social function measures
  - Dizziness
  - Gastrointestinal symptoms including nausea and vomiting (PROMIS gastrointestinal symptom scales)
  - Gastrointestinal symptom rating scale (before respiratory symptoms, many patients with COVID-19 had diarrhea, nausea, vomiting, abdominal discomfort)
  - Headache: headache impact test 6-item (HIT-6)
  - Anxiety: hospital anxiety and depression scale (HADS)
  - Fear/anxiety reported with SARS-CoV-2 infection (qualitative interview at baseline and recovery, GAD-7 scale value at all study visits [telephone or in person])

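### For patients already on oxygen at entry, incidence of new oxygen use is zero by design or depends on prior improvement, unless it is redefined as escalation

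*Protocol*

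**What the plan says.** **Endpoint.** Section 6.2 lists "Incidence and duration of new oxygen use during the trial". The synopsis objectives and Section 11.6.2 carry the same item, and none of the three defines new. The synopsis entry on efficacy endpoints is longer: "Incidence and duration of new oxygen use (e.g. oxygen insufflation, high-flow oxygen, non-invasive ventilation, mechanical ventilation, etc.) during the trial". A separate item, "Incidence and duration of new mechanical ventilation use during the trial", appears in the synopsis objectives and in Sections 6.2 and 11.6.2. The obesity objective in the synopsis and Section 11.6.2 also names new oxygen use as one of its outcomes.

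**Eligibility.** Section 7.1.2 sets "Requirement of oxygen support" as an inclusion criterion, and the synopsis does the same. Section 5.2 discusses a dexamethasone effect in patients on oxygen or invasive ventilation and adds: "Since only such patients will be eligible for this trial". Sub-study C requires "need for oxygen supplementation, non-invasive ventilation, high-flow oxygen devices or mechanical ventilation". For asunercept, Section 8.2 states that "only WHO scales 4, 5, and 6 are available for inclusion (patients with oxygen demand".

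**Analysis.** Section 11.6.2 reports incidence endpoints as frequencies per treatment group, with a logistic model adjusted for sex and age where appropriate. It describes all secondary analyses as exploratory.

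**The concern.** An incidence endpoint needs patients who are free of the event at baseline. Here the entry criteria remove them: everyone in the main study and sub-study C already needs the support whose first use is to be counted. Because new is not tied to the state at randomisation, the same daily records can give different results depending on whether first use, restart or escalation is counted. The trial is open label with interim looks, so that choice should not be left until data have been seen.

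Section 8.4 names avoidance of intubation as a possible benefit of asunercept and gives prevention of intensive care admission as a reason to continue the trial. An endpoint on worsening respiratory support should therefore be computable and should point in the right direction in the patients actually enrolled.

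**Working it through.** The protocol gives no rate, event count or power for this endpoint, so there is no figure to reproduce. The check sets the endpoint against the entry criteria, using the seven-category scale in Section 11.6.1: 3 is in hospital without oxygen, 4 on oxygen, 5 on non-invasive ventilation or high flow, 6 on invasive ventilation or ECMO.

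**Step 1. Who enters.** Sections 7.1.2 and 5.2 put main-study patients in category 4 or above. Section 8.2 puts asunercept patients in 4, 5 or 6. Pentaglobin patients also need some form of oxygen or ventilatory support.

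**Step 2. What can count as new, by category at entry.**

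| Entry category | First oxygen use | Restart after weaning | New, higher mode of support |
|---|---|---|---|
| 4 | impossible | only after reaching 3 or better | possible (to 5 or 6) |
| 5 | impossible | only after reaching 3 or better | possible (to 6) |
| 6 | impossible | only after reaching 3 or better | none left |

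**Step 3. What each reading gives.**
- *First use.* The at-risk set is empty. With the planned 100 per arm, the result is 0/100 against 0/100.
- *Restart.* A patient must improve before becoming at risk. If restarts were counted over all randomised patients, a treatment that weans more patients would put more of them at risk, so the count could move against the better arm. The protocol neither prescribes this reading nor gives rates for it.
- *Escalation.* Events are possible and arms can be compared. Only the synopsis efficacy-endpoint list supports this reading, and only through examples. Those examples include oxygen insufflation, which cannot be new for these patients, and mechanical ventilation, which is already a separate endpoint. No baseline level is named.

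**Step 4. New mechanical ventilation (illustration only).** Category 6 patients are already ventilated. Let *s* be their share and *p* the incidence among everyone else. If they stay in the denominator, reported incidence = *p* × (1 − *s*). Neither value is in the protocol. Assuming *p* = 20%:
- *s* = 10%: 20% × 0.90 = 18%
- *s* = 30%: 20% × 0.70 = 14%

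An absolute difference between arms shrinks by the same factor (1 − *s*). With equal *s* in both arms, the risk ratio is *p*₁(1 − *s*) / *p*₀(1 − *s*) = *p*₁ / *p*₀, which is unchanged.

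**The case against.** The strongest reply is that the synopsis does describe a usable endpoint, and that a short item elsewhere does not contradict a fuller one. On the synopsis list, a category 4 patient can newly start high flow, non-invasive or mechanical ventilation, and a category 5 patient can newly start mechanical ventilation. This stands. A reader might infer that the event can never occur and that no treatment comparison is possible; the protocol does not support that. It holds for the first-use reading alone.

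Other parts of the reply also stand:
- Oxygen-free days to day 29 remain informative, as does the duration component if taken as time on support.
- The endpoint list serves the whole platform. Sub-studies may take patients who miss the antiviral criteria, and sub-study B may take outpatients, so first oxygen use may be possible there.
- This is not the only measure of worsening. Mortality, intensive care admissions, ventilator-free days and daily WHO status are all listed.
- Secondary analyses are exploratory.
- No passage says that category 6 patients are counted for new mechanical ventilation. A denominator is ordinary SAP content, and Section 11 defers detail to the SAPs. A reader might take the dilution in Step 4 as an established loss; it is only what would follow under assumed shares and an unstated denominator.

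The reply does not remove the mismatch. Section 6.2, Section 11.6.2 and the synopsis objectives list an outcome whose plain meaning has no at-risk patients in the main study or sub-study C. The one passage that widens it keeps the impossible component and gives no reference level. Deferring detail to an SAP does not cure an endpoint that does not fit the protocol's own entry criteria.

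**Conclusion.** The point holds in a limited form. For main-study and sub-study C patients, incidence of new oxygen use is zero in every arm if it means first use, and arises only after improvement if it means restart. It is a usable measure of worsening only as escalation, which the synopsis suggests by example but no passage defines. This assumes that patients who need oxygen at entry are receiving it at randomisation.

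The consequence is modest: one exploratory secondary endpoint, and the obesity objective that reuses it, could be empty or misleading. The primary endpoint and its analysis are unchanged. The effect on new mechanical ventilation is illustrative, and a relative effect would be little affected. The change is still worth making because it replaces an unsuitable endpoint with one that fits the enrolled patients, at almost no cost.

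**What to change.** 1. For patients on oxygen or ventilatory support at entry, replace new oxygen use with incidence and duration of escalation of respiratory support above the level at randomisation: to WHO 5 or 6 for those entering in 4, and to 6 for those entering in 5.
2. Keep new oxygen use only for patients who enter without oxygen.
3. State that incidence of new mechanical ventilation is calculated among patients below WHO 6 at randomisation.
4. Use the same wording in the synopsis (objectives, including the obesity objective, and efficacy endpoints) and in Sections 6.2 and 11.6.2.

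Cost: wording only. Section 8.5.3 already provides for the WHO scale daily and for the mode of oxygen delivery as part of routine care. Treatment, visits and sample size do not change. The one drawback is a slightly smaller denominator for the ventilation endpoint.
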